### The intervention

The HMS BAB training is a competency-based training package developed by Jhpiego and Laerdal Global Health. The training programme has been designed to improve the knowledge and performance of delivery care providers through (1) an educational environment at the health facility level, with training conducted in health facilities; (2) an improved clinical practice environment, with material for practicing simulations provided in labour rooms; (3) monitoring quality improvement through ongoing data collection and feed-back analysis reports [30].

The training is provided by Jhpiego-accredited HMS BAB master trainers and is conceptualised to be relevant to all cadres of maternal care providers. The training lasts for approximately 4–6 h and is scheduled around the daily work of the staff. The curriculum includes theoretical and practical aspects of care, supported by pictorial flip-charts and MamaNatalie® birthing simulators, low-cost birthing simulators that can create normal and complex birthing scenarios. The birthing simulators are left in the facility after the training. The one-day training is followed by 8 weeks of in-service practice facilitated by clinical mentors. These mentors receive an additional half-day of training to guide the 8 subsequent weeks of peer practising using the MamaNatalie® birthing simulators. Mentors are supposed to organise and support these ‘low-dose, high-frequency’ weekly practice sessions which are anticipated to last 15–20 min each.

The curriculum of the main training includes (1) communication between staff and the mother, (2) preparation for a clean and safe delivery, (3) measuring blood loss, (4) checking the uterus tone postpartum, (5) routine care for mother and baby, (6) Active Management of the Third Stage of Labour (AMTSL), (7) cord cutting, (8) placenta delivery, (9) checking the placenta for completeness, (10) decision making and organisation of referral in case of complications, (11) assessment of tears as a cause of bleeding and (12) bimanual compression of the uterus. Much emphasis is placed on highlighting the provision of good care for the mother and the baby, thus the training links to the Helping Babies Breathe training. The curriculum does not cover more advanced emergency obstetric care interventions like manual removal of the placenta, balloon tamponade or surgical care.

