### Evaluation methodology

The evaluation is based on the primary outcome of severe maternal morbidity and several secondary outcomes which include preventive actions and case management of PPH; knowledge, skills and confidence in preventing and managing PPH; and facility readiness for prevention and care of PPH (Table 1). The evaluation uses the framework proposed by Kirkpatrick to assess training interventions along the pathway of impact from reaction, learning, behaviour and results [31]. We also assess the facility readiness — the capacity of the facility in terms of trained staff, equipment and supplies — to care for women with PPH, as this is likely to have an important impact on the application of the new knowledge and skills [32, 33].

**Table 1 Tab1:** Primary and secondary study outcomes

Primary outcome indicators	
Severe maternal morbidity	• PPH near-miss cases among all women who delivered in the facility • PPH near-miss cases among women who suffered PPH during health facility delivery • Near-miss cases among all women who delivered in the facility
Secondary outcome indicators	
Mortality (case fatality) in PPH near misses	• Deaths in PPH near-miss cases
Preventive actions and case management for PPH	• Proportion of women who received AMTSL of total women with PPH • Proportion of women with haemoglobin less than 70 g/L before discharge among those who suffered PPH • Proportion of women who received blood transfusion, intravenous oxytocin, balloon tamponade or a hysterectomy among those who suffered PPH • Proportion of women who need emergency transfer to a higher-level facility among those who suffered PPH in the health centre
Knowledge, skills and confidence in preventing and managing PPH	• Proportion of health care providers passing the knowledge test assessing preventive and emergency PPH care • Confidence score summing five questions about AMTSL, PPH, assessing advanced care, completeness of the placenta and bimanual uterine compression • Clinical skills score summing routine care including AMTSL, retained placenta and severe PPH • Team work
Facility readiness for prevention and care of PPH	• Proportion of facilities with AMTSL protocols and emergency tray available on day of visit • Proportion of facilities with at least a team of two midwives and one clinician on day of visit • Proportion of facilities with oxytocin and infusion set available in delivery room on day of visit • Stock-outs of oxytocin

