The primary outcome of this study is severe maternal morbidity defined by the WHO disease and management-based near-miss criteria and referring to women while pregnant or within 42 days of termination of pregnancy, excluding accidental or incidental cases [34]. We modified the original WHO definition criteria as proposed by Nelissen et al. [35] and supported by a recent study which indicated that restricting near misses to cases of organ dysfunctions excludes many severe cases, even in high-income settings like the Netherlands [36]. Thus we defined a near-miss case as a woman experiencing either eclampsia, sepsis or uterus rupture OR any organ dysfunction using the standard near-miss definitions OR having received blood transfusion or a hysterectomy. The indicators are constructed using the total number of deliveries reported by the facilities (indicators one and two). For indicator three ‘PPH-related near-miss cases among women who suffered PPH in health facility delivery’ we use the number of women experiencing PPH in the facility as the denominator. We measure case fatality in PPH near misses as a secondary outcome. Also, several secondary outcomes are selected to reflect knowledge and management along the pathway of implementation including equipment availability and supplies.

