## Data collection method

### Severe maternal morbidity and preventive actions and case management for PPH

We use the near-miss form as proposed by WHO to collect outcome data [34]. We include some background information, including use of induction/augmentation of labour, estimated blood loss and patient’s age and parity. We also added variables to capture the number of units of blood transfused and the haemoglobin at discharge for mothers who experienced haemorrhage or received a blood transfusion.

We trained two members of the maternity staff, midwives or clinicians, to be data collectors in each of the included health facilities. Their role is to abstract the relevant information each morning from the patient notes according to a standard protocol. Data collectors visit antenatal, labour and postnatal wards, the female general and female wards and the laboratory as well as attending the morning report session to ensure that all cases of near misses and female deaths are reviewed. All cases which could potentially qualify as a near miss are to be captured by the data collectors, including every case of haemorrhage regardless of the severity. Data are abstracted from multiple sources including admission, discharge and birth registries as well as case notes. The data collectors use a paper-based form and then enter the anonymised data immediately at discharge or death into the tablet-based application (Lenovo A3500-F). The application uses ranges and completeness checks to ensure data quality and completeness. The data collectors upload the data from the tablet to the cloud on a bi-weekly basis.

Training for data collectors is initially provided during a one-and-a-half day training session which includes (1) the concept of near miss, (2) collecting data using the near-miss forms and (3) the tablet application, procedure for uploading data, data safety and handling of missing data. We put an emphasis on the definition of PPH and its recognition in order to improve recording of PPH. Data collectors are retrained in a one-day refresher session after 5 months of data collection by reviewing forms with the data collectors and discussing their experiences and problems encountered.

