### Limitations

The main limitation of the study is that primary and secondary outcome measurements are not collected by external staff. We decided to use facility staff for several reasons: firstly ,we estimated that the time spent on collecting data in facilities would take less than 1 hour per day, which makes it unnecessary to employ external staff (and this would greatly increase costs); secondly, we received advice from local collaborators and district managers that the acceptability of external data collectors might be limited over such a long period of time; and thirdly, even if external data collectors were used, they would still rely on case notes prepared by maternity staff who are, by the nature of such a training intervention, not independent.

In order to address this, we aim to standardise the data collection during the 6-month period prior to the randomisation to reduce the reporting bias potentially introduced by the lack of blinding. In addition, our supervision team will visit the facilities every 1–3 months to verify the data by checking the registries. We also include an external assessment by independent data collectors in a sample of facilities to investigate any recording bias and confirm data completeness.

Another limitation is that the HMS training itself might improve recognition of PPH complications and recording of management. Such an unexpected reverse effect was observed in the evaluation of the Helping Babies Breathe training in Tanzania [11].

Contamination is a major threat to our evaluation. Other training or skill-building approaches in the field of safe motherhood or emergency obstetric care provided by the ministries of health or development partners might contaminate the training approach in our intervention and comparison districts. We are not able to restrict these much-needed development initiatives, as this would be unethical, but we document this when it occurs so that we are able to adjust for it in our analysis. Contamination and overall health sector development has been described in several trials to improve maternal and child health as a potential reason why results were missed [43, 44].

Finally, it is common practice that health workers are transferred to other facilities. In response, facilities in intervention districts might lose trained staff while facilities in comparison districts might then have health workers with improved skills to manage PPH.

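### Any blood transfusion alone makes a primary-outcome event, so readier recognition and treatment after the training could mask part of a real benefit, and the outcomes and checks described do not separate the two effects

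*Protocol article*

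**What the plan says.** Under Evaluation methodology, a near miss is eclampsia, sepsis or uterine rupture, or any organ dysfunction by the usual near-miss criteria, "OR having received blood transfusion or a hysterectomy". Each limb is sufficient alone, and the transfusion limb carries no minimum. Table 1 lists three primary indicators, beginning with "PPH near-miss cases among all women who delivered in the facility"; all three have a near-miss numerator.

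Under The intervention, the curriculum includes measuring blood loss and, as item "10) decision making and organisation of referral in case of complications". Transfusion is not among the twelve items, and "The curriculum does not cover more advanced emergency obstetric care interventions like manual removal of the placenta, balloon tamponade or surgical care".

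The Limitations section states: "Another limitation is that the HMS training itself might improve recognition of PPH complications and recording of management". It adds that an unexpected reverse effect was seen in an evaluation of Helping Babies Breathe. Its countermeasures are standardised data collection before randomisation, supervision visits that check the registries, and an external assessment in a sample of facilities.

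The data collection section says that variables were added to "capture the number of units of blood transfused and the haemoglobin at discharge". Analytical methods plans difference-in-differences on the proportion of near misses, with one subgroup (urban/rural).

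**The concern.** Receiving blood is partly a provider's decision: the bleed must be noticed, judged serious and acted on, or the woman referred. Take two women with the same bleed. One is recognised in a trained facility and given one unit; she is an event. The other is missed in a comparison facility and recovers without organ dysfunction; she is not. If the training shifts recognition in this way, better care is scored as more severe morbidity. The shift would arise after training and in the intervention arm only, so neither matching nor the baseline difference removes it.

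At stake is how the main result is read. A fall in true severity and a rise in appropriate transfusion would offset each other in one count. A small or null net effect could then be taken as failure of the training, or a net rise as harm.

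**Working it through.** **1. Do the described safeguards reach the problem?** Supervision, monthly reconciliation and the external review of registers and notes ask whether events were captured and correctly recorded. A real, correctly recorded transfusion passes all of them.

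**2. Do the secondary outcomes in Table 1 separate the two effects?**
- Transfusion appears as a process outcome, but pooled with intravenous oxytocin, balloon tamponade and hysterectomy, and only among women with recognised PPH.
- Haemoglobin below 70 g/L before discharge is itself changed by transfusion.
- Case fatality has PPH near misses as its denominator, so extra mild transfused cases make it look better.
- The primary indicator among women with PPH has a denominator that also grows with recognition, which pulls the other way.

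None isolates transfusion-only cases.

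**3. The plan's own sample size.** Inputs from Sample size: p0 = 0.02, p1 = 0.015, n = 3000, k = 0.15, z sum 1.96 + 0.84 = 2.80.

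Variance term V = p0(1−p0)/n + p1(1−p1)/n + k²(p0² + p1²) = 0.000006533 + 0.000004925 + 0.000014063 = 0.000025521.

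c = 2 + 2.80² × V/(p0 − p1)² = 2 + 7.84 × 0.000025521/0.000025 = 10.003; the article states 10. With 6% against 4.5% the formula gives 7.56, rounded up to the stated 8. Both reproduce.

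**4. Illustration of the masking.** Let s be the share of PPH near misses that qualify by transfusion alone, and m the factor by which the training multiplies those cases at a given severity. Neither is in the article; both are assumed. With a true 25% reduction:

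observed p1 = 0.015 × [(1 − s) + s × m]

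Power solves the article's formula for C clusters per group: Φ(√[(C − 2)(p0 − p1)²/V] − 1.96), with V recomputed at the observed p1. C = 10 is one country (Tanzania's ten per arm); C = 19 is both countries pooled (10 + 9 per arm).

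| s | m | observed p1 | rate ratio | apparent reduction | power, C = 10 | power, C = 19 |
|---|---|---|---|---|---|---|
| – | 1.0 | 0.01500 | 0.750 | 25% | 80% | 98% |
| 0.3 | 1.1 | 0.01545 | 0.7725 | 23% | 71% | 96% |
| 0.5 | 1.2 | 0.01650 | 0.825 | 17.5% | 48% | 79% |
| 0.7 | 1.3 | 0.01815 | 0.9075 | 9% | 16% | 29% |

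**5. When would the benefit vanish?** Observed p1 equals p0 when s(m − 1) = 1/3, so m − 1 = 1/(3s). Transfusion-only cases would have to rise by 111%, 67% or 48% for s = 0.3, 0.5 or 0.7.

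**The case against.** The strongest objection is that the broad definition is a reasoned choice. The article says that restricting near misses to organ dysfunction leaves out many severe cases. That stands, and it is why the definition should not be replaced.

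Second, the route is indirect. Transfusion is not taught and the intervention supplies no blood. The conceded limitation, "the HMS training itself might improve recognition of PPH complications and recording of management", concerns recognition and recording, not a lower threshold for transfusing. A reader might infer that the article admits a training-induced rise in transfusion and cites a precedent. It does not: Helping Babies Breathe is described as addressing neonatal care. What remains is a plausible path through recognition, decision making and referral.

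Third, the article mentions a separate analytical plan, which is not shown and could contain a component analysis. Its absence from the article is therefore not the fault. The point rests on an event definition, fixed here, that the intervention can move, and on a named threat answered only by measures that do not reach it.

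Fourth, the magnitude is wholly assumed. In the mildest scenario with both countries pooled, little is lost: 96% power against 98%.

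**Conclusion.** The point holds as a conditional threat to interpretation, and the supporting analysis should be added. Any transfusion suffices for a primary event, the training acts on steps that precede transfusion, and neither the described checks nor the listed outcomes distinguish more treatment from more severe disease. Under the assumed ranges the loss runs from slight to serious, as tabulated; the article's figures cannot say where the trial lies.

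A reader might infer that the objective on severe morbidity cannot be answered at all from the primary indicator. That is too strong: masking may be small or absent, and the intended effect (less bleeding, hence fewer transfusions) moves the same count downward. Nor is the direction uniform across the primary indicators, because of the growing denominator in the one restricted to women with PPH. The sample-size arithmetic itself is correct.

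**What to change.** Keep the near-miss definition as primary. Pre-specify a supporting analysis that splits PPH near misses per facility delivery into:

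- (a) organ dysfunction, uterine rupture, hysterectomy or death;
- (b) transfusion only, described by units given.

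State where a woman with PPH who qualifies only through eclampsia or sepsis is placed. Report both components by arm with the same difference-in-differences method as the primary.

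Fix the reading in advance. A rise in (b) accompanied by a fall in (a) will not be read as harm or as absence of effect. An unchanged (a) is reported as no demonstrated effect on that component, with its confidence interval. The rule must not excuse an unchanged (a), since that would shield a null result.

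The cost is analysis wording only. Units transfused are already recorded, and the other components are needed to apply the definition. The downside is that (a) has fewer events and a wider interval, omits some severe cases that the article wants counted, and still includes hysterectomy, also a provider's decision. It therefore supports the primary and does not replace it. Specified only after results are known, the same split would look like a rescue.

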## Abstract

**Background:**

Postpartum haemorrhage complicates approximately 10% of all deliveries and contributes to at least a quarter of all maternal deaths worldwide. The competency-based Helping Mothers Survive Bleeding after Birth (HMS BAB) training was developed to support evidence-based management of postpartum haemorrhage. This one-day training includes low-cost MamaNatalie® birthing simulators and addresses both prevention and first-line treatment of haemorrhage. While evidence is accumulating that the training improves health provider’s knowledge, skills and confidence, evidence is missing as to whether this translates into improved practices and reduced maternal morbidity and mortality. This cluster-randomised trial aims to assess whether this training package — involving a one-day competency-based HMS BAB in-facility training provided by certified trainers followed by 8 weeks of in-service peer-based practice — has an effect on the occurrence of haemorrhage-related morbidity and mortality.

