Several competency-based training packages are currently employed in low-resource settings. One example is the *Helping Babies Breathe* training package, which addresses neonatal care. Evaluations of this package have shown a positive effect on providers’ competence and on neonatal mortality and stillbirth rates [10–12], though not in all settings [13, 14]. Another example is the *PRONTO* (*Programa de Rescate Obstétrico y Neonatal: Tratameniento Óptimo Y Oportuno*) competency-based training package. This package showed an effect on reducing neonatal mortality in Mexico [15] and resulted in improved use of evidence-based interventions, patient-centred care and teamwork in Guatemala [16]. The *Making it Happen* programme, a comprehensive simulation and competency-based emergency obstetric care training, was very well received by health providers and demonstrated improvements in knowledge and competence of providers [17, 18].

The *Helping Mothers Survive Bleeding after Birth* (HMS BAB) training programme is a one-day competency training specifically addressing basic skills to prevent and treat PPH [19, 20]. The training is conceptualised to build the capacity of teams of obstetricians, midwives and other health care providers attending births. Recent studies have shown this HMS BAB training to have an impact on knowledge and confidence among health care providers [21, 22]. While evidence on the effect on health outcomes of competency-based training, especially the Helping Babies Breathe training, is accumulating, there is no evidence of the effect of the HMS BAB training on health outcomes. It is also unknown whether health system challenges, such as lack of equipment and supplies, counteract the effectiveness of such a training programme.

This study evaluates the effect of the HMS BAB one-day competency-based in-facility training followed by 8 weeks of in-service practice along the impact pathway, including the health outcomes of morbidity and mortality in the two low-resource settings of Tanzania and Uganda. We will specifically assess the effect of the training on (1) severe maternal morbidity and mortality due to PPH, (2) preventive actions and case management of PPH, (3) knowledge, skills and confidence in preventing and managing PPH and (4) facility readiness, including equipment and supplies, for prevention and care of PPH.

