## Discussion

The evaluation will estimate the effect of the HMS BAB training on maternal mortality and morbidity (near-miss) in a large two-country trial. The study will provide evidence on whether the training programme leads to improved maternal health outcomes. We will also be able to provide information on ’lessons learned’ in implementing the training including the 8-week in-service practice sessions which at medium scale can be used to guide future policy and investments regarding scale-up of training programmes for maternal health in the respective countries. Looking at the evaluation along the implementation pathway will allow us to propose some explanations in case we unexpectedly see no effect of the intervention.

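### The aims name an effect on mortality, but the only mortality outcome is case fatality among PPH near misses, which cannot estimate an effect on the occurrence of death

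*Protocol article*

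**What the plan says.** Three places in the protocol article name mortality as something the trial will assess. The Abstract (Background) asks whether the package "has an effect on the occurrence of haemorrhage-related morbidity and mortality". The first objective in the Background section is "severe maternal morbidity and mortality due to PPH". The Discussion goes further: "The evaluation will estimate the effect of the HMS BAB training on maternal mortality and morbidity (near-miss) in a large two-country trial".

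Table 1 has one mortality row, headed as case fatality, with one indicator: "Deaths in PPH near-miss cases". The text under Evaluation methodology confirms it: "We measure case fatality in PPH near misses as a secondary outcome". No listed outcome counts deaths per delivery or per woman with PPH.

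The first-listed primary indicator in the same table is "PPH near-miss cases among all women who delivered in the facility", so the numerator of the primary outcome is the denominator of the mortality outcome. The Sample size section assumes that training lowers it by 25%, from 2% to 1.5% of deliveries.

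On data, data collectors make daily rounds "to ensure that all cases of near misses and female deaths are reviewed", and they record haemorrhage cases of every severity. Facility delivery totals are obtained monthly and verified at supervision visits.

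**The concern.** An effect on the occurrence of death is a comparison of deaths among the women at risk, here those delivering in the study facilities. Case fatality among near misses conditions on an event that happens after randomisation and that the training is meant to reduce. Even with perfect randomisation, the women in the denominator are then not comparable between arms, and the ratio mixes the effect on deaths with the effect on near misses.

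The denominator is also open to recording differences. Near-miss status depends partly on receiving a transfusion, the data collectors are facility maternity staff who know the allocation, and the Limitations section accepts that training may improve recognition of PPH and recording of its management.

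At stake is the answer to the mortality part of the first objective. As the outcomes stand, no mortality effect with its own confidence interval would be reported, and the one figure labelled mortality could point the wrong way.

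**Working it through.** **Inputs.** From the Sample size section: control PPH near-miss rate 2%, assumed reduction 25%, 3000 deliveries per cluster, k = 0.15, z values 1.96 + 0.84. From Study design and methodology: 10 pairs in Tanzania and 9 in Uganda. From the Background: at least 1 haemorrhage death per 1000 women. That last figure is a general floor and not a facility rate, so I use it only as an assumption, with a range of 0.5 to 2 per 1000.

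**The plan's own figure.** For PPH near misses:

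- c = 2 + 2.8² × [0.02×0.98/3000 + 0.015×0.985/3000 + 0.15²×(0.02² + 0.015²)]/0.005² = 10.003; the plan states 10.
- The same formula with 6% and 4.5% gives 7.56; the plan states 8.

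The sample size reproduces. It shows that the plan is built on a 25% fall in this denominator.

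**The ratio.** Let D and M be deaths and near misses per delivery in the comparison arm, and let training reduce them by fractions d and m. With no other difference between arms:

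case-fatality ratio = [D(1-d)/(M(1-m))] / (D/M) = (1-d)/(1-m)

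D and M cancel, so the baseline death rate does not matter. The ratio of deaths per delivery is 1-d.

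| Near misses | Deaths | Case-fatality ratio | Deaths-per-delivery ratio |
|---|---|---|---|
| fall 25% | fall 25% | 0.75/0.75 = 1.00 | 0.75 |
| fall 25% | unchanged | 1/0.75 = 1.33 | 1.00 |
| fall 25% | fall 50% | 0.50/0.75 = 0.67 | 0.50 |
| recorded cases rise 20% (assumed) | unchanged | 1/1.20 = 0.83 | 1.00 |

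The first row hides a benefit, the second makes no effect look like harm, the third understates a benefit, and the fourth creates one.

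**In counts.** Ten clusters × 3000 = 30,000 deliveries per arm, so 600 v 450 near misses. At an assumed 1 death per 1000, a 25% fall gives 30 v 22.5 deaths. Case fatality is 30/600 = 5.0% and 22.5/450 = 5.0%.

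**Precision of deaths per delivery.** These figures ignore clustering.

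- Ten pairs: SE of the log rate ratio = √(1/30 + 1/22.5) = 0.28. A ratio of 0.75 has a 95% interval of about 0.43 to 1.30.
- At 0.5 per 1000 (15 v 11.25 deaths) the SE is 0.39; at 2 per 1000 (60 v 45) it is 0.20.
- All 19 pairs at 1 per 1000 (57 v 42.75): SE 0.20, interval about 0.50 to 1.12.
- Power for a 25% fall at 1 per 1000 is about 18% with 30,000 deliveries per arm and 30% with 57,000.

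**The case against.** The best defence is that the protocol labels the outcome openly as case fatality and reports it beside near misses per delivery. If every PPH death also meets a near-miss criterion, as the wording of the row suggests, then deaths per delivery equal the near-miss rate times case fatality. A careful reader of the equal-fall example would see 25% fewer near misses, unchanged case fatality, and hence 25% fewer deaths. The same deaths would also count in the primary indicator. This stands as far as it goes, but it leaves the reader to construct the estimate, it depends on that condition, and it supplies no planned confidence interval.

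It is also fair that case fatality is a legitimate measure of management once a near miss has occurred, that the outcome is secondary, and that deaths per delivery would be too imprecise to settle the question. All of that stands. Low power is no reason to prefer case fatality, which rests on the same deaths and answers a different question.

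A reader might infer more than the documents support:

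- **That training removes milder near misses first, leaving a sicker denominator and a higher case fatality.** No part of the protocol says so, and the recognition effect in the Limitations section works in the opposite direction.
- **That the trial will report no effect, or harm, on mortality.** That depends on how deaths and near misses actually move, which is unknown.
- **That case fatality will be about 5%.** This divides a background floor by a planning assumption. The Background's own companion figure of 30 further severe morbidities per 1000 would give roughly 3%.

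**Conclusion.** The mismatch is real. The aims name an effect on mortality, and the only mortality indicator cannot estimate an effect on the occurrence of death. Under the protocol's own 25% assumption, the case-fatality ratio is the true mortality ratio divided by 0.75, or 1.33 times too high. If recorded near misses rose by 20%, it would be 0.83 of the true ratio. The direction of the distortion therefore cannot be known in advance.

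The algebra assumes arms that are otherwise comparable and needs no death rate. The counts and standard errors rest on an assumed 1 death per 1000 deliveries and ignore clustering. The primary outcome and the sample size are not affected. The issue should be corrected, but it concerns one secondary outcome and the wording of the aims.

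**What to change.** Add one row to Table 1: PPH-related deaths among all facility deliveries, as a secondary mortality outcome. Compare it at district level within matched pairs by the approach already planned for the other outcomes, report it with a 95% confidence interval, and state that the trial is not powered for it. Pooling the two countries is not needed for this correction.

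Keep case fatality among PPH near misses, described as a measure of case management and not as the mortality effect. It need not be replaced. The Discussion sentence speaks of maternal mortality in general, so its wording should be brought into line with the outcome that is added.

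The cost is small, because deaths and delivery totals are already collected. The downside is one more imprecise secondary outcome, introduced while endline data collection is under way in Tanzania. The date and reason for the addition should be disclosed.
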